### Post-treatment procedures (rehabilitation program)

The participants will be discharged 1 h after injection of the cell suspension or LP-PRP solution and advised to rest for 48 h. Analgesia (ibuprofen 600 mg, every 8 h, and omeprazole 20 mg once daily) are prescribed for the participant to self-administer if needed.

After treatment, a specific rehabilitation protocol will be followed, applying appropriate progressive load to the affected limb [6]. Table 1 shows the rehabilitation program over 3 months. For greater details, please refer to Malliaras et al 2015 [15] and Mascaro et al. 2018 [47].

**Table 1 Tab1:** Rehabilitation program over 3 months

Rehabilitation program	Day 0–3	4–5 days	2–3 weeks	4–8 weeks	3 months
RICE					
Isometric squat against wall		5 reps × 30–40 s (3’ rest). Progress from 45° to 90° knee flex)			
Cycling (alternate days)			15–30 min	15 min	
Isometric leg extension 30°			8 reps × 45'' (1’ rest)		
Elliptical training (alternate days)				15 min	
Slow dynamic knee extension (Con/Ecc)				4'' Con/4'' Ecc, 30'' rest. Increase load from 2 to 12 kg. Progress from bilateral to unilateral	
Numeric rate score (NRS) allowed				< 4/10, if > 4/10 stop progression load for 2–3 days	
Running					Progressively
Plyometrics					Progressive jumps landing to plyometrics. Every 3 days
Fast dynamic exercise (Con/Ecc)					3 × 6–8 reps, 1–3' rest

After the 3 months, and after evaluating each patient by physical examination, US and MRI, the athletes will be progressively allowed to gradually return to their sport.

The follow-up consists of clinical examination visits and image monitoring by ultrasonography and by UTC, MRI-UTE, as specified in the protocol schedule.

### Concomitant medications

Any concomitant medications administered from the day of the initial treatment until the end of the trial will be recorded. No fluoroquinolone-based antibiotic drugs will be administered during the entire study period [48, 49]. If they must be administered, the subject will be excluded from the clinical trial and will continue therapy using standard treatments. Corticosteroids or anti-inflammatory therapy should not be administered. If they must be administered, the patient will not be excluded from the trial, but the administration will be recorded in the clinical records. If necessary, treatment with ibuprofen 600 mg will be allowed.

### Response evaluation

Subsequent assessments following the treatment include AE review, VAS (pain), VISA-P Questionnaire, ultrasound imaging (conventional ultrasound, UTC and MRI), dynamometry manual test and clinical assessment (Table 2 for phase A, and Table 3 for phase B). These will take place at 1, 2, 3, 6, 8 and 10 weeks and 3, 6, 12 months post-treatment.

**Table 2 Tab2:** Outcome assessments experimental phase A

Study period															
	Enrollment				Treatment		Follow-up								
Timepoints					0	23 days	1 week	2 weeks	3 weeks	6 weeks	8 weeks	10 weeks	3 months	6 months	12 months
Inf. sheet	X														
Incl/excl Criteria		X													
IC		X													
Preop + serology			X												
Allocation				X											
ClinicalHistory	X	X													
Physical exam	X	X					X	X	X	X	X	X	X	X	X
VAS		X					X	X	X	X	X	X	X	X	X
VISA-P		X					X	X	X	X	X	X	X	X	X
blood test													X		
Group MSV BM					X										
Group MSV saline sol.					X										
Group MSV MSV						X									
Group PRP BM sham					X										
Group PRP PRP					X	X									
Bloodbank					X										
MRI		X											X*		X
Ultrasound		X					X	X	X	X	X	X	X	X	X
UTC			X						X		X		X	X	X
DYN			X						X		X		X	X	X
AE					X	X	X	X	X	X	X	X	X	X	X
Medication					X	X	X	X	X	X	X	X	X	X	X

*Elig.* eligibility, *IC* informed consent; *VAS* visual analogue scale; *VISA-P* Victorian Institute of Sport Assessment (Patellar); *BM* bone marrow harvest; MSC Infusion of MSC; *MRI* magnetic Rresonance; *UTC* ultrasound tissue characterisation; *DYN* dynamometry, *PreOp* preoperative study, *AE* Adverse Events.

*X** if the *VAS* and *VISA-P* scales show a significant improvement, and *MRI*, *US*, and UTC provide evidence of healing, the result will be considered positive and the patient will be followed up with confirmation controls at 6 and 12 months. For safety reasons, according to AEMPS criteria, a control test will be performed after the trial, within a period of 2 years after treatment.

If the 6-month evaluation shows negative results, patients may be transferred to the open experimental phase B.

**Table 3 Tab3:** Outcome assessments experimental phase B

Study period															
	Enrollment			Treatment		Follow-up									
Timepoints				0	23 days	1 weeks	2 weeks	3 weeks	6 weeks	8 weeks	10 weeks	3 months	18 weeks	6 months	12 months
IC		X													
Preop + serology			X												
Physicalexam	X	X				X	X	X	X	X	X	X	X	X	X
VAS		X				X	X	X	X	X	X	X	X	X	X
VISA-P		X				X	X	X	X	X	X	X	X	X	X
blood test												X			
BM				X											
MSV					X										
Bloodbank				X											
MRI		X										X*	X	X	X
Ultrasound		X				X	X	X	X	X	X	X	X	X	X
UTC			X					X		X		X	X	X	X
DYN			X					X		X		X	X	X	X
AE				X	X	X	X	X	X	X	X	X	X	X	X
Medication				X	X	X	X	X	X	X	X	X	X	X	X

*VAS* visual analog scale; *VISA-P* Victorian Institute of Sport Assessment (Patellar); *BM* bone marrow harvest; *MSV* injection of *MSV*; *MRI* magnetic resonance imaging; *UTC* ultrasound tissue characterization; *DYN* dynamometry, *PreOp* preoperative study, *AE* adverse Events.

*X** this MRI test will establish the status of the healing process at 3 months.

### Adverse events

Possible adverse events occurring during the trial period (regardless of whether they are related to the procedure) will be recorded and tabulated. In the event of a serious adverse effect, a notification will be sent to the Spanish agency for Medicines and Healthcare Products (AEMPS) through the Clinical Research Organization (CRO), according to established procedures and terms.

### Pain and function

Pain will be recorded on the VAS, and function will be evaluated by measuring extension forces in the knee using a manual dynamometer.

The pain and functional evaluation will be performed using the VISA-P score, which specifically evaluates pain and function in patellar tendinopathy. The scale ranges from 0 to 100, where a value of 100 indicates the absence of pain at rest, when walking, when climbing up or downstairs or during exercise [50]. VISA-P score values for patients with chronic patellar tendinopathy usually range from 30 to 50. Physical activity may be undertaken again if values are above 60. Patients with score values over 70 are considered fit for competition, although demands are higher for professional athletes. The minimum significant difference has been set at 13 points.

The following VISA-P criteria are used to assess improvement in this trial [51]:
Desired: ≥ 60/100 (after 3 months)Very satisfactory: ≥ 70/100 (after 6 months)Ideal: ≥ 80/100 (after 12 months)

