### Criteria for non-response to treatment

A lack of response to treatment will be recorded if no clinically relevant improvement or tendon repair changes occur after a 6-month period. Clinical changes will be assessed using a combination of physical examination, VAS score, VISA-P questionnaire and DYN. Tendon repair will be assessed using ultrasonography, UTC and MRI. A partial response will be considered if there is evidence of either clinical improvement or tendon repair.

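### VISA-P improvement is judged by absolute scores of 60, 70 and 80 that ignore baseline and are not reconciled with the protocol's own 13-point minimum difference

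*Protocol article*

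**What the plan says.** The section 'Pain and function' gives two yardsticks for the VISA-P. The first is a change: "The minimum significant difference has been set at 13 points". The second is a set of levels, introduced by "The following VISA-P criteria are used to assess improvement in this trial" and listed as "Desired: ≥ 60/100 (after 3 months)Very satisfactory: ≥ 70/100 (after 6 months)Ideal: ≥ 80/100 (after 12 months". The same section says of the starting point that "VISA-P score values for patients with chronic patellar tendinopathy usually range from 30 to 50", and of the instrument that "The scale ranges from 0 to 100". It also ties scores above 60 to resuming physical activity and scores over 70 to fitness for competition. It does not say how the 13 points and the three levels work together.

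Other sections depend on what improvement means:

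- 'Criteria for non-response to treatment' says "A lack of response to treatment will be recorded if no clinically relevant improvement or tendon repair changes occur after a 6-month period", and then "Clinical changes will be assessed using a combination of physical examination, VAS score, VISA-P questionnaire and DYN". Imaging is used for tendon repair, and a partial response is allowed.
- 'Experimental phase B' bases the later offer of cell therapy partly on the absence of clinically relevant improvement. The abstract words the same offer as failure to reach a satisfactory primary endpoint at 6 months.
- Table 2 of 'Response evaluation' ("Outcome assessments experimental phase A") collects the VISA-P at enrolment and at every follow-up visit, so change from baseline can be computed for each patient.
- The inclusion and exclusion criteria set no VISA-P limit.
- 'Statistical analysis' compares groups and time points by repeated-measures ANOVA, by ANCOVA if covariables with a significant interaction are found, or by rank tests. It does not use the levels.

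**The concern.** A criterion for improvement should respond to change. These criteria respond only to where the patient ends up, and the required end point rises from visit to visit. A patient who starts low can gain several times the minimum difference and still fall short. A patient who starts high can meet the 3-month criterion with a gain below that difference, or with none.

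At stake is the label attached to each patient. 'Clinically relevant improvement' is the abstract's first aim, a component of the 6-month non-response label, and part of the condition for the phase B offer. On the VISA-P it could mean a gain of 13 points or a score of 70 at 6 months, and these can pick out different patients. With ten patients per arm, one relabelled patient moves any reported proportion improved in that arm by 1/10, or 10 percentage points.

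**Working it through.** The article gives no expected VISA-P gain, standard deviation or responder rate, so there is no figure of its own to reproduce. Steps 1 and 2 use only its numbers. Steps 3 and 4 add assumptions, which are stated.

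**Inputs, all from 'Pain and function':** levels 60, 70 and 80 at 3, 6 and 12 months; minimum difference 13; usual scores 30 to 50, taken as a proxy for baseline; scale 0 to 100.

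**Step 1. Gain needed = level − baseline, compared with 13.**

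| Visit | Level | From baseline 50 | From baseline 30 | Multiple of 13 |
|---|---|---|---|---|
| 3 months | 60 | 10 | 30 | 0.8 to 2.3 |
| 6 months | 70 | 20 | 40 | 1.5 to 3.1 |
| 12 months | 80 | 30 | 50 | 2.3 to 3.8 |

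Under a 13-point rule the score needed would run from 30 + 13 = 43 to 50 + 13 = 63, the same at every visit.

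**Step 2. Where the two yardsticks disagree.**

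- From 50 to 60 at 3 months: gain 10, below 13, yet the level is met. In general 60 − baseline < 13 for any baseline above 47.
- Entry at 60 or more and no change: gain 0, yet the 3-month level is met. The entry criteria do not exclude this.
- From 30 to 69 at 6 months: gain 39 = 3 × 13, yet the level is missed.

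**Step 3. Share meeting each level at a fixed gain g, assuming baseline uniform on 30 to 50.** Share = (50 − (level − g)) / 20, held between 0 and 1. For g = 13 and level 60: (50 − 47) / 20 = 15%.

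| Gain | 60 at 3 months | 70 at 6 months | 80 at 12 months |
|---|---|---|---|
| 13 | 15% | 0% | 0% |
| 20 | 50% | 0% | 0% |
| 30 | 100% | 50% | 0% |
| 40 | 100% | 100% | 50% |
| 50 | 100% | 100% | 100% |

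**Step 4. Share of patients gaining at least 13 who miss the level, when gains vary.** Simulation of 1,000,000 patients per scenario: baseline uniform on 30 to 50 or normal (mean 40, SD 10); gain normal with mean 10 to 40 and SD 10, 15 or 20; follow-up score held to 0 to 100. Example rows for the uniform baseline and gain SD 15:

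| Mean gain | Miss 60 | Miss 70 | Miss 80 |
|---|---|---|---|
| 10 | 37.8% | 74.6% | 92.6% |
| 20 | 27.2% | 60.6% | 84.3% |
| 30 | 16.3% | 42.6% | 69.3% |
| 40 | 7.5% | 24.0% | 48.1% |

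Over all scenarios the share is about 4% to 51% at 3 months, 19% to 89% at 6 months and 45% to 99% at 12 months. In the other direction, among patients at 60 or more at 3 months, the share with a gain below 13 is 0% to 4.5% with the uniform baseline and up to about 22% with the normal one.

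**The case against.** The strongest reply is that a minimum difference and a target level are different quantities and can coexist. The labels *Desired*, *Very satisfactory* and *Ideal* read as graded goals, and two of them match functional states that the section describes. A goal set well above the smallest change that matters is not an error. This stands as far as it goes: a reader might infer that the protocol contradicts itself, and that is too strong. What remains is that the text calls these levels the criteria for assessing improvement and does not link them to the 13 points.

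A reader might also infer that the levels misclassify most patients who improve. The document does not support this. It states no expected gain or spread, and the share depends on the visit and the assumed gain. In the scenarios above it exceeds half at 12 months for mean gains up to 35, at 6 months mainly for mean gains of about 25 or less, and at 3 months only for mean gain 10 with SD 10.

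A third inference is that a patient stable at 65 passes at 3 months and fails at 6, so that planned responder rates would shift. No section calls a score below 70 a failure. Non-response rests on four clinical measures together with imaging, and allows a partial response. The analysis section names no VISA-P responder analysis, and its group tests do not use the levels. This objection stands and limits the point to labelling.

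Entry at 60 or more may be uncommon, given a usual range of 30 to 50 and the requirement of more than four months of symptoms with no relevant response to conservative treatment. It is possible under the entry criteria, not shown to be frequent.

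Finally, the full protocol may explain how the two yardsticks combine. But the article does more than leave this open: it states a rule, and as stated the rule can count zero change, or change below the minimum difference, as improvement.

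**Conclusion.** The point holds in a limited form. The stated VISA-P criteria for improvement are attained levels that ignore baseline, and they are not reconciled with the protocol's own 13-point difference. Within the usual range of 30 to 50 they ask for 20 to 40 points at 6 months and 30 to 50 at 12 months, while at 3 months 10 points can suffice. Those figures are plain arithmetic. They rest only on taking the usual range as the baseline, which is not an entry criterion. The number of patients whose label would change cannot be derived from the document.

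The consequence is that 'clinically relevant improvement' has no single VISA-P meaning in the sections that use it. The planned between-group tests are not affected by the cut-offs.

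**What to change.** 1. For outcome reporting, define VISA-P improvement as a gain of at least 13 points from the patient's own baseline, at every visit.
2. Report the proportions at or above 60, 70 and 80 separately, as attained states.
3. Compare groups on the VISA-P with prespecified adjustment for baseline VISA-P, instead of using ANCOVA only if a covariable interaction proves significant.
4. Reconcile the abstract, 'Experimental phase B', 'Pain and function' and 'Criteria for non-response to treatment' on what 'clinically relevant improvement' and a 'satisfactory' result mean. Which rule should govern the phase B offer is for the investigators. This review does not propose one.

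The cost is wording in the protocol and analysis plan; the data are already scheduled. There are two downsides. 'Trial Status' shows all 20 patients recruited by 28 October 2018, so the change must be dated and documented before unblinded analysis or it will look post hoc. And a 13-point gain can count a patient who is still below the activity level of 60 (from 30 to 43, for example), which is why both measures should be shown together.

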### Ultrasonography

Ultrasound scanning will be performed with an Aplio 500 (TUS-500 5.0 Platinum Series, manufactured by Canon Medical Systems Corporation in Nasu, Japan) using a high-frequency linear array probe (PLT 1005BT), 5.0–14 MHz frequency range. The most commonly used 2D frequency will be differential harmonic of 14 MHz (diff THI 14 MHz). The depth used will be 5 cm, with a single focus at 1.8 cm and a dynamic range of 65 dB

The patellar tendon will be examined longitudinally and transversely using greyscale and colour measures, exerting the least possible pressure with the probe. Images will be recorded in static and dynamic formats.

Therapeutic results will be regarded as positive if the following findings will be evidenced: improvement in tendon echotexture, gap reduction and reduced neovascularization.

A change in thickness will also be considered, but to a lesser extent, as the significance of thickness change in terms of success of any intervention programme is unknown [44].

The following will be determined:
Lesion location (medial, central, lateral) and (anterior, central, posterior).Tendon thickness 5 mm distal to the inferior pole of the patella.Eco-texture (using a 0–3 scale).Longitudinal and axial “gap” measures; area value.Vascularization degree I–V

### UTC

Tendon eco-structure will be evaluated according to four subtypes I, II, II and IV in cross-section of region of interest (ROI): percentage of each subtype will be calculated. The distance (mm) from the lower patellar pole in the anteroposterior section and cross-section will also be measured (based on percentage points).

Subtype I is regarded as ideal, corresponding to a perfectly aligned fibrillar structure; Subtype IV is regarded as the most sub-optimal, corresponding to the absence of fibrillar structure. To establish a healing standard, the 4 aforementioned subtypes will be assessed, and changes will be evaluated by calculating the relative increase in percentage points of subtypes I and II (indicative of organised tissue), along with the relative decrease in percentage points of subtypes III and IV (indicative of disorganised tissue).

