UTC is an innovative imaging technique for assessing tendon injuries. Using a conventional ultrasound device, 600 axial sections of the tendon are performed at 0.2 mm intervals and compounded to form a 3D image. Using this technique, collagen fibre alignment may be quantified into four different types: (a) normal aligned fibrillar structure; (b) slightly misaligned fibrillar structure; (c) disorganised fibrillar structure; (d) complete disintegration of tendon tissue [43]. Ultrasonography is the most accessible imaging technique used to confirm the clinical diagnosis and determine the exact location of the lesion. Ultrasonography also helps calculate tendon size, defines eco-texture, allows measurement of any tendon gaps in several planes and assesses the degree of tendon vascularization. In addition, ultrasonography allows to dynamically monitor tendon function [44].

Should the results be better for the cell therapy group, the patients in the active control group (who were injected with LP-PRP) who have not achieved similar benefits to those of patients in the MSC group after 6 months will be offered cell therapy. We believe that this will increase the feasibility of the clinical trial.

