### Statistical analysis

Statistical analysis will be performed using version 21. 0 of the Statistical Package for Social Sciences (SPSS Inc, Chicago, IL). We will evaluate: (i) adverse events (AE) and serious adverse events (SAE) showing relationships, causality and severity will be provided; (ii) frequency and percentage of AE and SAE; (iii) laboratory results including hematologic and biochemistry values will be collated: leukocytes levels, absolute neutrophils count, platelet count, creatinine levels, AST (SGOT)/ALT (SGTP) levels, etc. A list of laboratory parameters will be obtained for each patient and visit and will include reference range values. Values will be summarized in a basal and post-basal visit analysis will include the following values: (i) valid ‘n’; (ii) mean; (iii) standard deviation; (iv) median; (v) minimum and maximum.

The frequency and percentage values of patients showing evidence of tendon regeneration 6 months after treatment with MSC or P-PRP will be provided.

The following methods will be used to describe and analyse the results obtained:
Descriptive statistics in numerical variables: number of valid cases; number of non-available values; mean value; standard deviation; 95% confidence interval for the mean value; median, minimum and maximum values. In discrete and categorical variables, the following values will be provided: frequency; percentage value for the total number of valid cases; percentage value for the total number of non-available values.Inferential statistics tests for comparing groups and time points: ANOVA with repeated measures (or ANCOVA) if covariables with a significant interaction are detected with their corresponding contrast values (Scheffe test), or non-parametric tests if the assumption of normality is rejected (Mann-Whitney *U* test for comparison between groups and Wilcoxon test for comparison between measurements). The significance level for all statistical analyses will be 0. 05.

Efficiency sample (per protocol (PP) population) includes all patients whose tendon lesion has been treated with an MSC or LP-PRP suspension. These patients must have had no major violations of the protocol, and at least one assessment of efficacy after treatment.

‘Full analysis set’ (FAS) (intention to treat analysis) includes all patients in the study, whether they finish the study or comply with the protocol.

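### The UTC healing measure mixes a relative and an absolute scale, splits one change into two complementary figures, and does not assure adjustment for baseline

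*Protocol article*

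**What the plan says.** The Background explains that with UTC "collagen fibre alignment may be quantified into four different types", running from normally aligned to fully disintegrated. The UTC section states that within the region of interest the "percentage of each subtype will be calculated". It then gives the purpose of the change measure: "To establish a healing standard, the 4 aforementioned subtypes will be assessed". Healing is expressed as a "relative increase in percentage points of subtypes I and II (indicative of organised tissue), along with the relative decrease in percentage points", where the second part refers to the disorganised tissue, III+IV. It gives no denominator, threshold or rule for combining the two figures.

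The section on criteria for non-response names UTC once among the imaging methods: "Tendon repair will be assessed using ultrasonography, UTC and MRI". The Statistical analysis section compares groups and time points by "ANOVA with repeated measures (or ANCOVA) if covariables with a significant interaction are detected", with rank tests if normality is rejected. Table 2 schedules UTC before treatment, at 3 and 8 weeks, and at 3, 6 and 12 months.

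**The concern.** UTC is one of the named tools for the second main objective, which is whether tendon structure regenerates after MSC and not after LP-PRP. Its change measure therefore has to have one meaning. As worded, it can be read on two scales and is given in two complementary forms.

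On the relative reading, the size of a patient's improvement depends on where the patient started and on which form is quoted. A favourable version could then be picked after the data are seen. On the percentage-point reading, the two forms coincide, but nothing ensures that the comparison allows for baseline. With 10 patients per arm, sizeable chance differences in baseline are to be expected.

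**Working it through.** **Inputs.** From the protocol article: four UTC subtypes as percentages of one region of interest, 10 patients per arm, significance level 0.05. Assumed, because the article gives no UTC values: the four percentages sum to 100, and all baseline values, SDs, correlations and gains below. The article states no UTC figure that could be reproduced.

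**Step 1: the two measures are complements.** Let B be the baseline percentage of I+II and g the gain in percentage points. Then III+IV starts at 100 - B and falls by exactly g.

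- Percentage-point reading: rise in I+II = g and fall in III+IV = g, the same number.
- Relative reading: rise in I+II = g/B and fall in III+IV = g/(100 - B). Their ratio is B/(100 - B), which equals 1 only at B = 50.

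**Step 2: a 10-point gain on the relative reading.**

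| Baseline I+II | I+II | III+IV |
|---|---|---|
| 40 | 10/40 = +25% | 10/60 = -16.7% |
| 50 | 10/50 = +20% | 10/50 = -20% |
| 60 | 10/60 = +16.7% | 10/40 = -25% |
| 80 | 10/80 = +12.5% | 10/20 = -50% |
| 90 | 10/90 = +11.1% | 10/10 = -100% |

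**Step 3: where the two relative versions part.**

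- *Within a patient*, g has one sign, so the directions always agree.
- *Ranking of patients.* From 50 to 58 gives +16% and -16%; from 80 to 86 gives +7.5% and -30%. The first patient does better on I+II, the second on III+IV.
- *Arm means.* Take two patients in one arm, 40 to 48 and 85 to 80. For I+II: (20% - 5.9%)/2 = +7.1%, an improvement. For III+IV, 60 to 52 and 15 to 20: (-13.3% + 33.3%)/2 = +10%, a worsening.

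**Step 4: the percentage-point reading still leaves baseline unadjusted.** With equal SD σ at baseline and follow-up and correlation r, a change score has SD σ√(2(1 - r)), and the ANCOVA residual has SD σ√(1 - r²). With σ = 10:

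| r | Change score | ANCOVA |
|---|---|---|
| 0.4 | 10.95 | 9.17 |
| 0.6 | 8.94 | 8.00 |
| 0.8 | 6.32 | 6.00 |

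If the arms differ by 8 points at baseline and treatment has no effect, regression to the mean shifts the difference in change by (1 - r) × 8, which is 3.2 points at r = 0.6.

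**Step 5: illustrative power.** Simulation with baseline mean 75, SD 10, true gain 8 points, 10 per arm; t-tests on change against ANCOVA.

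| r | Relative I+II | Absolute change | ANCOVA |
|---|---|---|---|
| 0.4 | 0.31 | 0.34 | 0.44 |
| 0.6 | 0.44 | 0.47 | 0.54 |
| 0.8 | 0.71 | 0.75 | 0.77 |

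At r = 0.6, relative III+IV has power of about 0.40, and the two relative versions disagree on significance in about 21% of trials. Under no effect and no imposed imbalance, rejection is about 5% for relative I+II and 4% for relative III+IV. With an imposed 8-point baseline imbalance at r = 0.6, relative and absolute I+II change each reject in about 0.095 of trials, against 0.05 for ANCOVA.

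**The case against.** The strongest reply is that percentage points are an absolute unit, so the sentence may simply describe one shift in composition from both sides. The problem of different denominators then disappears. This stands: the text does not settle the relative reading, and the figures in steps 2 and 3 hold only under it.

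A reader might go further and infer any of three things, none of which the article supports:

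- *That one change is counted twice in the response decision.* No rule adds, scores or tests the two figures separately, and the response criteria list UTC once. Double counting is a risk that the wording leaves open, not a stated procedure.
- *That the two versions can contradict each other for a single patient.* Their directions always agree; only size and ranking differ.
- *That the relative scale inflates false positives.* Overall it does not. The excess appears only given a baseline imbalance, and absolute change shares it.

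It is also fair to say that the article does not name a t-test on change. With one baseline and one follow-up visit, however, the group-by-time test of repeated-measures ANOVA is the t-test on absolute change. The simulation is therefore relevant to the named method, although it does not represent a model with all visits. Finally, details of adjustment are often left to the analysis plan, and this is a pilot that admits limited power. But the article does fix a change measure, and it makes ANCOVA conditional on a significant interaction. Both are open to comment as written.

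**Conclusion.** The point holds as a defect of definition with a modest statistical cost. The UTC change measure combines two incompatible scales and presents two complementary figures, of which the second carries no independent evidence if the subtypes sum to 100%. On the relative reading, the two figures for one change differ by a factor of B/(100 - B), for example 4 at a baseline of 80. On the percentage-point reading they are identical.

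On either reading, baseline adjustment is not assured. Under the assumed values, moving from relative to absolute change adds 0.03 to 0.04 to power. Moving from absolute change to ANCOVA adds 0.10, 0.07 and 0.02 at correlations of 0.4, 0.6 and 0.8. Most of the benefit at the two lower correlations thus comes from adjustment rather than from dropping the relative scale. The power figures rest on invented baseline values and illustrate the direction and rough size only. The algebra rests only on the four percentages summing to 100.

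**What to change.** In the UTC section, replace the two-sided relative wording with one measure: the percentage of subtypes I+II in the region of interest at 6 and 12 months. Compare arms by ANCOVA with baseline I+II as a covariate that is always included, whatever any interaction test shows. Report the adjusted difference in percentage points with a 95% CI. Keep III+IV as a descriptive summary, not as separate evidence of healing. Bring the Statistical analysis section into line, so that ANCOVA for this outcome no longer depends on a significant interaction.

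The cost is a short change of wording and one residual degree of freedom (17 instead of 18 with 20 patients). No new data are needed, since UTC is already scheduled before treatment and at 6 and 12 months.
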